#### Repeated measures modeling

For the primary and secondary outcomes, repeated measures will be used in a linear mixed model. ANOVA with time (T0-T1-T2) as a within-groups component and treatment condition as a between-groups factor will be utilized. Mixed-model repeated measures ANOVA does not substitute missing values; it uses all the data for each participant that are available. We’ll run a sensitivity analysis to examine the effect of drop-outs on our findings. The full data sets of participants who finish all sessions of the training will be the basis for the protocol analysis. The time to onset of clinical outcomes will be based on post-training interview and two follow-up assessments. The pooled standard deviations will be used to calculate the effect sizes (Cohen’s d) within and between groups. Appropriate statistical tests will be used to explore differences between intervention and control groups (Fisher’s exact test as appropriate). The nature of the routine administrative data will determine the test’s selection. SPSS statistics, Excel, and Visual Basic for Applications will be used for all analyses (VBA).

The multilevel analysis will be used with nested data to account for clustering and adjust for the type of critical incident, age, and sex. Means and standard deviations for continuous outcomes and proportions for categorical outcomes will be reported.

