### Setting and participants

Hospitals will be chosen to ensure sufficient number of clusters. In China, we contacted 73 public hospitals and health centers in six provinces of Hunan, Hainan, Xinjiang, Fujian, Dalian, and Jiangxi, presented the study to their staff members, and invited them to participate. Forty-two agreed to participate. The randomization was at the hospital cluster-level which to ensure minimal contamination. The hospitals will be randomly allocated to one of two groups (the PFA training group or the control training as usual group) with a ratio of 1:1 with stratification by hospital type (primary, secondary). The randomization will be conducted by an independent administrator at CADERM not associated with the study using a block-randomization schedules provided by the study statistician. The potentially eligible subjects will be invited to participate via a text message after informed consent is obtained from all participants.

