### Study procedure

Participants will receive face-to-face or online one-day training intervention including six sessions, with follow-up assessment at 1 and 2 months after training. Before the training, participants will be selected for study eligibility according to the study’s inclusion and exclusion criteria. They will be evaluated by a research staff blinded to the intervention in each hospital. After the selection, participants will be assigned to one of the two groups and informed by message about their training (place and time). Groups of participants will receive training according to their random assignment group. There will be three assessment points for the intervention and control groups: (1) immediately post training, (2) one month post training, and (3) two months post training. Assessments will be undertaken remotely, with online instruments. An overview of the protocol procedure is provided in Figure 1.

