C1: Statement of foundations	There should be a clear statement of the key concepts and principles of the general mental health training	Is there a clear statement of the mental health concepts and training content?
C2: Statement of application/perspective	The application of the common psychological treatment and mental health interventions (conditions and timing) should be stated clearly and the application should be consistent with the stated principles and overall objective of the training	Are the primary recipients specified? Is the application of the training consistent with the stated principles? Has the application of the training been stated and justified? Are the outcomes of the training consistent with the perspective, application and overall objective of training?
C3: Rational for the structure	The structure of the training should be consistent with a coherent theory of the mhGAP, and the guideline should be followed to implement the interventions The structure should be dictated by current patterns of service provision All sources of evidence used to develop and inform the structure of the training (i.e., the theory of behavior based treatment) should be described. The structure should be consistent with the objective of the training.	Has the evidence regarding the training structure been described? Is the structure of the training consistent with a coherent theory of psychological therapy and mental health interventions in disasters and emergencies? Are the sources of evidence used to develop the structure of the training specified?
C4: Strategies/techniques	The training should include possible options that represent current good practice Trauma rehabilitation interventions in disasters and conflicts Psychological debriefing or critical incident stress debriefing (CISD)	Are there clear definitions of incorporated techniques? Have all feasible and practical options been introduced? Is there justification for the exclusion of feasible options?
Balint groups for medical practitioners	To help medical practitioners to reflect their practice and reconsider the emotional relationship with the patients	Have the Balint group process and techniques been described and referenced in sufficient detail?

Outcomes.

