### Analysis

#### Data analysis

Statistical analysis will be performed using STATA (version 17 or later) and a *p*-value < 0.05 (two-tailed) will be taken to indicate statistical significance.

All trial participants who were randomly assigned at the start of the trial will stay in the sample for analysis under the intention-to-treat principle. It will be decided whether the intervention program is effective using random effect mixed modeling described below. Demographic factors will be evaluated for their potential influence on primary and secondary outcomes, and in cases where they do, they will be used as covariates.

The primary outcome for the statistical analysis will be the mean change in PFA-SKA score after 2 months of follow-up compared between intervention and control arms. The analysis allowed for this clustering in order to obtain unbiased estimation of the treatment effect and its standard error (SE). A two-level hierarchical mixed-effects model will be used to be fitted in the statistical analysis plan.

All secondary outcomes will be summarized by trial allocation group and follow-up period using mean, SDs and 95% CIs for the variables (ProQOL, GSE, PTGI scores). Statistical tests of differences for secondary outcomes will be performed using the same hierarchical mixed-effects model as the primary outcome analysis. In addition, participant-scores are also compared as change from post-training to 2-month follow-up using independent group t-tests.

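### The stated adjustment set leaves out the stratification factor, stands beside a second outcome-driven covariate rule, and includes an undefined covariate

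*Protocol article*

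**What the plan says.** In the protocol article, Setting and participants allocates hospitals "with a ratio of 1:1 with stratification by hospital type (primary, secondary").

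Three statements in the analysis sections then bear on the model.

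- **Data analysis, model form:** "A two-level hierarchical mixed-effects model will be used to be fitted in the statistical analysis plan". Secondary outcomes are to be tested with the same hierarchical model as the primary.
- **Data analysis, covariates:** "Demographic factors will be evaluated for their potential influence on primary and secondary outcomes, and in cases where they do"; any such factor is then adjusted for. No list of factors and no criterion is given.
- **Repeated measures modeling:** "ANOVA with time (T0-T1-T2) as a within-groups component and treatment condition as a between-groups factor will be utilized". The same section then fixes an adjustment set: "The multilevel analysis will be used with nested data to account for clustering and adjust for the type of critical incident, age, and sex".

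Study procedure puts every listed assessment after training: "There will be three assessment points for the intervention and control groups: (1) immediately post training, (2) one month post training, and (3) two months", the last also counted from the training. Populations under investigation says that missing data will be removed by listwise or pairwise deletion, and also that the multilevel model uses all available data.

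**The concern.** Three things do not fit together.

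First, hospital type shapes the randomisation but is not among the stated model terms. Stratified allocation makes the arms more alike than simple randomisation would. A model without the factor does not credit this, so its standard error is too large. With only 42 hospitals, cluster-level precision matters.

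Second, age and sex are demographic factors. One section always adjusts for them, while the other adjusts only if they show influence on the outcome. An analyst cannot follow both rules. The second rule also lets observed outcome data decide which model gives the primary estimate.

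Third, the type of critical incident is a covariate without a definition. If it was recorded at the listed assessments, it was measured after randomisation and training. A participant who had no incident could have a blank and be dropped under the deletion rule, contrary to the intention-to-treat statement in Data analysis.

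**Working it through.** **Inputs.** From Sample size: d = 0.43, ICC = 0.2, 21 hospitals per arm, 30 participants per hospital, power 0.80, alpha 0.05, 10% dropout. From Data analysis: two-sided testing. Total variance is set to 1. The share R of between-hospital variance explained by hospital type is not in the article; it is an assumption, varied over 0, 10, 20 and 40%.

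**Step 1: the plan's own figure.** An individually randomised trial needs 85 per arm. The design effect is 1 + 29 × 0.2 = 6.8, so 85 × 6.8 = 578 per arm, and 578/30 = 19.3 hospitals. With a t reference distribution, 20 hospitals per arm give power 0.795 and 21 give 0.815, so 21 is the smallest number that reaches 0.80. Then 42 × 30 = 1260, and 1260/0.9 = 1400 (or 1260 × 1.1 = 1386), against the stated 1399. The sample size reproduces and is not at issue.

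**Step 2: standard error.** The variance of a hospital mean is 0.2 + 0.8/30 = 0.2267 without the factor and 0.2(1 − R) + 0.8/30 with it. The standard error of the arm difference is √(2 × variance/21). The ratio is the standard error with the factor divided by the one without it.

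| R | Variance | SE | Ratio |
|---|---|---|---|
| 0 | 0.2267 | 0.147 | 1 |
| 10% | 0.2067 | 0.140 | 0.955 |
| 20% | 0.1867 | 0.133 | 0.907 |
| 40% | 0.1467 | 0.118 | 0.804 |

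**Step 3: type I error with the factor omitted.** Under stratified allocation the estimate varies with the smaller standard error, but the test uses the larger one. The error is therefore close to 2 × P(t with 40 df > 2.021/ratio). This gives 2.021/0.955 = 2.12 and 4.1%; 2.021/0.907 = 2.23 and 3.2%; 2.021/0.804 = 2.51 and 1.6%. Simulation of 42 hospital means, balanced within type, gives about 4.0 to 4.2%, 3.1% and 1.5%. With the factor included, the error stays at about 5%.

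**Step 4: power.** With the factor included, a noncentral t with 39 df gives 0.848, 0.882 and 0.944. With it omitted, the baseline is not the 0.815 of Step 1, because stratified balance already makes the true variance smaller. Simulation gives the omitted column.

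| R | Omitted | Included | Loss, points |
|---|---|---|---|
| 0 | 0.81 | 0.81 | 0 |
| 10% | 0.82 to 0.83 | 0.85 | about 2 |
| 20% | 0.83 to 0.84 | 0.88 | about 5 |
| 40% | 0.86 | 0.94 | about 8 |

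The results hardly change between a 50/50 and a roughly 25/75 split of hospitals by type (also an assumption). They rest on equal cluster sizes and a single time point.

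**Step 5: the two covariate rules.** Under Repeated measures modeling, age and sex always enter. Under Data analysis, they enter if they show influence, and so may any other demographic factor. If that rule is applied outcome by outcome, the covariates can differ between outcomes, which conflicts with the same section's promise of one model for the primary and secondary outcomes. With neither a factor list nor a criterion, the effect on the estimate cannot be put into numbers.

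**Step 6: the critical-incident covariate.** As a participant variable it appears only in the adjustment sentence. Eligibility requires no incident. The only other critical-incident wording is a technique in the control-arm fidelity checklist (Table 2): "Psychological debriefing or critical incident stress debriefing (CISD").

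**The case against.** The strongest objection is that the article condenses a fuller plan. Data analysis refers the model to a statistical analysis plan that is not shown, and the adjustment list is not called exhaustive; a stratification term could well be there. This would be decisive if the article were silent on covariates. But it states a set, and that set lacks the design factor. Hospital type is also a cluster attribute, not a participant demographic, so the selection rule does not naturally bring it in.

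Second, the omission is benign in direction. That stands. A reader might infer a biased effect, an inflated alpha or power below target. None follows: the error is conservative, and power stays above the planned 0.80 in every case examined.

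Third, the Blinding section keeps statisticians blinded and gives them de-identified data. This limits choosing a model by its treatment effect. It does not say which model is primary.

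Fourth, a reader might infer that the type of critical incident is not collected, or that it is certainly measured after randomisation. The questionnaires are not shown. The PTGI asks about a crisis, so an event type might be recorded beside it, and that event could predate randomisation. The article supports only that no definition and no collection are described.

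Fifth, a reader might infer that each outcome will certainly have its own model. The same-model sentence speaks against this; what remains is a conflict between two sentences.

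**Conclusion.** The point holds in a limited form. The stated adjustment set omits the factor used to stratify randomisation, two covariate rules are unreconciled, and one named covariate is undefined.

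The cost of the omission depends on how much between-hospital variance hospital type explains, which the article does not give. Over the assumed range of 10 to 40% it is about 2 to 8 points of power, with type I error at about 4% down to 1.5%; at 0% there is no cost. The covariate-rule conflict is certain from the text, but its numerical effect is unknown. The risk from the critical-incident covariate (adjustment for a post-randomisation value, and loss of participants with blanks) is conditional on when and for whom it is recorded. This should be corrected before analysis; it does not undermine the design or the sample size.

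**What to change.** 1. Include hospital type as a fixed effect in the primary and secondary models.
2. State one covariate set for all outcomes (hospital type, age, sex), and delete the rule that admits demographic factors by their observed influence.
3. Remove the type of critical incident from the efficacy model, unless it is defined as a variable fixed before randomisation and recorded for every participant.

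The cost is analysis wording and one cluster-level degree of freedom (39 instead of 40). If hospital type explains nothing, power stays at about 0.81. No extra hospitals, participants or assessments are needed.

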#### Populations under investigation

Any participant with any post-baseline follow up will be included in the modified intention to treat (ITT) population. We will remove the missing data from analyses using listwise or pairwise deletion. A multilevel multivariable linear model does not substitute missing values; it uses all of the data for each participant that are available. The full data sets of participants who finish all sessions of the training and respond to the first round interview will be the basis for the protocol analysis.

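### The rule that missing data are removed by listwise or pairwise deletion contradicts the available-data mixed model and leaves the primary analysis set unsettled

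*Protocol article*

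**What the plan says.** The Protocol article makes five statements about who and what enters the analysis.

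- Data analysis: "All trial participants who were randomly assigned at the start of the trial will stay in the sample for analysis under the intention-to-treat principle".
- Populations under investigation, opening sentence: "Any participant with any post-baseline follow up will be included in the modified intention to treat (ITT) population".
- Same section, second sentence: "We will remove the missing data from analyses using listwise or pairwise deletion".
- Same section, third sentence: "A multilevel multivariable linear model does not substitute missing values; it uses all of the data for each participant that are available".
- Repeated measures modeling: "Mixed-model repeated measures ANOVA does not substitute missing values; it uses all the data for each participant that are available". It then adds: "We’ll run a sensitivity analysis to examine the effect of drop-outs on our findings". The method of that sensitivity analysis is not given.

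The quantity these rules govern is set in Data analysis: "The primary outcome for the statistical analysis will be the mean change in PFA-SKA score after 2 months of follow-up compared between intervention and control". Study procedure schedules three assessments, all after training (immediately, at one month and at two months), done remotely with online instruments. Repeated measures modeling labels the time points T0, T1 and T2.

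**The concern.** A likelihood-based mixed model and listwise deletion are different ways of handling missing scores. The model keeps a participant who has only some of the three scores, and uses those scores to inform the two-month comparison. Listwise deletion removes that participant altogether. A plan that states both, in adjacent sentences, does not say which set of participants produces the primary result. The choice between listwise and pairwise is also left open, and the two can yield different samples.

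What is at stake is bias more than precision. Health workers who stop answering online questionnaires may differ in score from those who continue, and may do so differently by arm. If their earlier scores predict non-response, keeping those scores protects the comparison under a missing-at-random assumption, and listwise deletion throws that protection away.

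The term post-baseline adds a second uncertainty. No assessment before training is scheduled, so T0 may be taken as the baseline. A participant with a T0 score and nothing later would then be excluded from the modified ITT set, yet would be kept under the Data analysis section and by the available-data model.

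**Working it through.** **1. The rules side by side, for a participant with some scores missing**

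| Scores present | All randomised (Data analysis) | Modified ITT, if T0 is baseline | Listwise deletion | Available-data model |
|---|---|---|---|---|
| T0, T1, T2 | in | in | in | in |
| T0 and T1 only | in | in | out | in |
| T0 only | in | out | out | in |
| none | in | out | out | contributes nothing |

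The rows that separate listwise deletion from the available-data model are the partial responders. The last row shows that some modification of all-randomised is unavoidable in any likelihood analysis without imputation.

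**2. The planned sample size, reproduced**

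Inputs from Sample size: d = 0.43, ICC = 0.2, power 0.80, alpha 0.05, 21 clusters per arm, 30 per cluster, 10% for drop-out. Alpha is two-sided (Data analysis).

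- Without clustering: 2 × ((1.960 + 0.842)/0.43)² = 85 per arm, rounded up.
- Design effect: 1 + (30 − 1) × 0.2 = 6.8, so 85 × 6.8 = 578 per arm, or 578/30 = 19.3 clusters.
- With a noncentral t on 2k − 2 degrees of freedom, power is 0.795 at k = 20 and 0.815 at k = 21. So 21 clusters per arm is the minimum.
- 42 × 30 = 1260. Then 1260/0.9 = 1400, or 1260 × 1.1 = 1386. The stated 1399 is consistent with these.

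**3. Effect of losing participants on power**

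SE = sqrt(2 × DE/(k × m)), with k = 21, DE = 1 + (m − 1) × 0.2, and m = 33.3 × (1 − loss), where 33.3 = 1399/42. The loss rates are assumed, apart from the planned 10%.

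| Loss | Participants left | DE | SE of d | Power |
|---|---|---|---|---|
| 10% | 1259 | 6.79 | 0.147 | 0.815 |
| 20% | 1119 | 6.13 | 0.148 | 0.809 |
| 30% | 979 | 5.46 | 0.149 | 0.802 |

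With an ICC of 0.2, the number of hospitals drives the SE, and losing members within hospitals changes it little.

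**4. How far the analysed sets could differ (illustration)**

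The document gives 10% as drop-out per cluster and says nothing about the pattern over visits.

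- If the same 10% are missing throughout, or leave and never return, complete cases are 90%: 0.9 × 1399 = 1259.
- If 10% are missing independently at each of three visits (a heavier loss, assumed), complete cases are 0.9³ = 72.9%, about 1020. At least one score is available for 1 − 0.1³ = 99.9%, about 1398.
- T0-only participants: 0.9 × 0.1 × 0.1 = 0.9%, about 13, under that independent pattern. If the whole 10% left between T0 and T1, they would be about 140.

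**5. Can the deletion rule bias the comparison? (simulation, all inputs assumed)**

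True d = 0.43 at each visit, unit SD, no clustering, 400,000 simulated participants. In the control arm the chance of missing T2 depends on the T0 score, as Φ(−1.1 − 0.8 × T0), giving about 20% loss. In the intervention arm it is unrelated to score, about 14% loss.

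| Correlation between visits | Complete cases | Using the T0 score of everyone |
|---|---|---|
| 0.5 | 0.33 | 0.43 |
| 0.7 | 0.28 | 0.43 |

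The second estimate regresses T2 on T0 among completers within arm and predicts for all. The simulation shows that bias is possible and that retained T0 scores can remove it. Because missingness was made to depend only on an observed score, it says nothing about the size or direction to expect in this trial.

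**The case against.** The strongest reply is that the deletion sentence may only mean that nothing is imputed. The sentence after it says that missing values are not substituted, and dropping empty visit records is what a mixed model does anyway. The sentence might also be meant for the t-tests on change from post-training to two months, which need both scores. Either reading is possible, but the text does not state it. The rule is said to apply to analyses in general, it directly follows the modified ITT definition, the per-protocol set is defined separately, and listwise is named. In a repeated-measures setting, listwise means complete cases.

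Several other points stand and limit the concern.

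- A modified ITT set is openly labelled as such, and a participant without any score adds nothing to the model. A reader might infer that the ITT claim is simply untrue. The document supports only that its statements do not fit together.
- A reader might infer that deletion is valid only if data are missing completely at random. That is too strong: complete-case regression is also valid when missingness depends only on covariates in the model, and the plan adjusts for age, sex and type of incident. Bias needs missingness related to the score given those covariates.
- If non-response depends on the unseen score, the mixed model is biased too. Deleting the sentence is not a complete cure.
- A drop-out sensitivity analysis is promised, and the Blinding section keeps the statisticians blinded, which limits any choice of deletion rule to favour an arm. Neither settles which rule is primary.
- How the sensitivity analysis is carried out may properly be left to the statistical analysis plan.

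**Conclusion.** The point holds as an internal contradiction about the primary analysis. The deletion sentence conflicts with the sentence after it and with Repeated measures modeling, and it does not fit the promise that all randomised participants stay in the sample. This is not detail left to a later plan: the article states the conflicting rules itself.

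If the rule is applied as listwise, the analysis becomes one of complete cases and may be biased when non-response is related to earlier scores. The document gives no basis for the size or direction of that bias. The loss of power is small: 0.815 at 10% loss and 0.802 at 30%, on the plan's own d, ICC and number of clusters.

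A reader might infer that more than a quarter of participants would be lost at the planned drop-out. The document does not support this. The 73% complete-case figure assumes 10% missing independently at each of three visits, which is a heavier loss than the planned 10%; the same 10% missing throughout leaves 90%. The simulated shifts from 0.43 to 0.33 or 0.28 are likewise illustrations under chosen inputs. The case for change rests on the contradiction and the possibility of bias, not on these figures.

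**What to change.** - Delete the sentence on listwise or pairwise deletion.
- Define one primary set: all participants of the randomised hospitals, analysed by allocated arm, with every available score entering the likelihood-based multilevel mixed model. At least one of T0, T1 and T2 is enough to contribute. Replace the post-baseline condition with this wording, and report by arm how many participants have no score at all.
- State that the primary analysis assumes data are missing at random given the observed scores and the covariates in the model.
- Keep complete cases as a supplementary analysis only.
- Say that the drop-out sensitivity analysis already promised will examine departures from missing at random. Delta-adjusted imputation that respects the clustering is one option; others would serve.

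The cost is a few sentences and a little more analysis. Design, sample size and data collection are unchanged. The wording should be settled before outcome data are analysed.
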